– There is limited quantitative data to support dose-volume models for the kidney. Studies are required with collection of data that would allow correlating regional kidney function over time with the radiation dose distribution received in the radiotherapy treatment.

– The glomerular filtration rate (GFR) should be used to assess the toxicity of the kidney, as recommended by the National Kidney Foundation [9]. Early changes in renal perfusion and GFR correlate with an increased risk of late toxicity [2] and chronic injury is unlikely if changes in GFR and perfusion are not detected by 24 months after irradiation [10,11].

– Significant technological advances in imaging offer the possibility to study late responding normal tissues using quantitative functional imaging instead of a conventional histological analysis [12].

GFR can be estimated using serum creatinine levels and estimating equations but in order to achieve a higher degree of accuracy, a ^51^Cr-ethylenediamine tetra-acetic acid (EDTA) clearance measurement should be used. On the other hand, scintigraphy with Single Photon Emission Computed Tomography (SPECT) can provide greater detail regarding the relative distribution of kidney function; kidney perfusion as indicated by uptake of ^99m^Tc-dimercaptosuccinic acid (DMSA), imaged with scintigraphy, has been shown to correlate with relative regional function [13,14]. Sequential GFR measurements using the ^51^Cr-EDTA clearance and SPECT imaging undertaken before, during and after radiotherapy, allows observation of regional functional changes in the kidney over time and these changes can be correlated with the radiation dose delivered during radiotherapy.

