### Study hypotheses

An assessment of changes in total kidney function (using GFR measurement), regional kidney functional change (using SPECT imaging) and their correlation with radiotherapy dose delivery is within the means of currently available imaging, therapy and computational technology. The hypotheses being tested in RAPRASI are:

– Temporal variations in SPECT images of the kidneys correlate with patterns of radiation dose delivery in the kidneys.

– Models of kidney response developed from SPECT-response studies can be used to predict changes in kidney function as a result of radiation therapy.

The principal aim of RAPRASI is to obtain a better understating of kidney response when a patient is receiving radiotherapy for an upper-abdominal cancer. This will involve monitoring the spatial and temporal changes in kidney function for correlation with delivered three-dimensional radiation dose distribution. A more precise dose-volume response model for kidney will not only improve our current understanding but may permit further optimisation of radiation therapy techniques for upper-abdominal tumours.

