### Data collection and quality assurance

This study will be conducted according to the Human Research Ethics Committee (HREC)-approved study protocol and the ‘Note for Guidance on Good Clinical Practice (CPMP/ICH/135/95) annotated with TGA comments’ (Therapeutic Goods Administration DSEB July [18]. The study will be performed in accordance with the NHMRC ‘National Statement on Ethical Conduct in Human Research’ (© Commonwealth of Australia 2007) and the ethical principles within the ‘Declaration of Helsinki’ (Revised 1996) [19].

Sir Charles Gairdner Hospital will act as the sponsor of this study at both the Peter MacCallum Cancer Centre and Sir Charles Gairdner Hospital in Perth, Western Australia. Standard medical care (prophylactic, diagnostic and therapeutic procedures) remains the responsibility of the patient’s treating physician.

The investigator is responsible for ensuring that no participant undergoes any study related examination or investigations prior to obtaining written informed consent. The investigator will explain the aims, methods, possible benefits and potential hazards before the participant gives consent. The participant will be given sufficient time to read the documentation, understand the project and have any questions addressed prior to signing the consent form. The participants will be advised that they have the right to withdraw their consent to participate at any time without any consequences.

Participant confidentiality will be protected at all times. In any resulting publication or presentation, no patients will be identified.

Records will be retained for 15 years post study completion in a locked facility, in accordance with TGA requirements. Access to participant study records will be limited to treating clinician, chief investigator, his/her nominated co-investigators and the local study co-ordinators.

Collation of data will yield the following for each participant:

– Local kidney function/response to therapy: regional change in SPECT signal intensity:

•from baseline to 4 weeks post start of radiotherapy

•from baseline to 12 weeks post start of radiotherapy

•from baseline to 26 weeks post start of radiotherapy

•from baseline to 52 weeks post start of radiotherapy

•from baseline to 78 weeks post start of radiotherapy

– Planned 3D Regional radiation dose distributions intended to be experienced during radiation treatment.

– Kidney function measure: GFR at baseline, 4, 12, 26, 52 and 78 weeks.

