– Indication of existing and acquired co-morbidities.

– Information on adjuvant treatments.

GFR measurements using the ^51^Cr-EDTA clearance and Digital Imaging and Communication in Medicine (DICOM) formatted SPECT/CT images will be obtained on Siemens Symbia T6 SPECT/CT scanners located in the Department of Nuclear Medicine at SCGH and the Centre for Molecular Imaging at the PMCC. These images involve pre-injection of approximately 185 MBq of ^99m^Tc-DMSA (Radpharm DMS 1987/1), providing 128x128 pixel attenuation-corrected images reconstructed at approximately 5 mm pixel resolution. SPECT images are automatically registered to CT taken on the same device (6 slice helical CT scanner), with image settings sufficient for organ definition and bone matching with minimal radiation dose (typically 130 kV, 80-100 mA, 5 mm slice thickness). SPECT pixel intensity values will be normalised according to calibration images obtained on the scanner during monthly quality-assurance checks. SPECT data will be reconstructed using an ordered subset expectation maximization (OSEM) algorithm incorporating CT attenuation data.

Treatment plan data (images, structures, beam definitions, dose-volume data, and 3D dose distribution) will be exported in DICOM-RT format from the Treatment Planning System. (CMS XiO at SCGH, Varian Eclipse at PeterMac). Digitally reconstructed radiographs (DRRs) will be generated indicating local bony anatomy (upper pelvis, spine, ribs) and the location of kidneys from the planning CT. Variation in kidney position relative to local bony anatomy is of the order of SPECT image resolution [20,21]. Patient localisation will initially be to external marks, with on-line positioning then corrected according to localisation images spatially matched to the DRRs. Localisation images will be obtained either with the Brainlab Exactrac system (6D patient positioning) [22] or the Varian On-Board Imaging system (3D positioning) [23]. Applied patient shifts will be recorded together with localisation images. Where possible, kidney position will be identified on the localisation images for comparison with planned kidney outlines, as per standard departmental practice.

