### Data analysis

To correlate the patterns of change in SPECT signal with time relative to delivered dose distributions, SPECT signal intensity will be used as a measure of local renal function – a change in this measure is an indication of ‘renal response’. This response needs to be correlated with regional radiation dose distribution. Planned 3D radiation dose distributions will be digitally registered with kidney functional changes in order to generate dose response models. The planning CT will be registered to the initial SPECT/CT data for definition of baseline kidney location and function. Subsequent SPECT/CT data (intensity-normalised according to administered nuclide activity) will be registered both using bone anatomy as well as SPECT intensity distribution providing registration of radiation dose distribution and SPECT signal. All imaging shall be performed with the patient in the same position on a flat-topped couch, allowing quantification of changes in kidney positioning in the abdomen relative to the planned dose distribution. Co-registrations will be made using the Velocity AI software [24]. Velocity’s deformable image registration will allow subsequent SPECT images to be deformable registered to the baseline SPECT/CT, on the basis of both CT anatomy and SPECT signal, and for all co-registered data sets to be deformable registered to the planned 3D dose distribution. This will allow subsequent SPECT images to be deformable registered to the baseline SPECT/CT, on the basis of both CT anatomy and SPECT signal, and all co-registered data sets to be deformable registered to the planned 3D dose distribution (or vice-versa), exported from the Treatment Planning System in DICOM-RT format. Applying these methods to data collected during the RAPRASI study will allow accurate spatial registration of regional changes in SPECT signal to planned radiotherapy dose. The method of registration to obtain correlated SPECT/dose is shown on Figure 2.

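### Follow-up SPECT is aligned to baseline partly on the SPECT signal that is itself the outcome, and the 4-week scan may be paired with planned dose not yet delivered

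*Protocol article*

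**What the plan says.** **Registration.** The Data analysis section treats a change in SPECT intensity as the renal response. It states twice that Velocity's deformable registration will allow "subsequent SPECT images to be deformable registered to the baseline SPECT/CT, on the basis of both CT anatomy and SPECT signal". It also says that follow-up data will be registered on bone anatomy and on the SPECT intensity distribution.

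**Dose.** Study hypotheses sets the aim as "correlation with delivered three-dimensional radiation dose distribution", and Data analysis opens with the intention to "correlate the patterns of change in SPECT signal with time relative to delivered dose distributions". The dose item collected per participant is different: "Planned 3D Regional radiation dose distributions intended to be experienced during radiation treatment". The modelling sentence agrees with that item, not with the aim: "Planned 3D radiation dose distributions will be digitally registered with kidney functional changes in order to generate dose response models". No dose received by the date of a scan is defined.

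**Timing.** Study design and schedule counts the visits at 4, 12, 26, 52 and 78 weeks from the first fraction, and the first response interval runs "from baseline to 4 weeks post start of radiotherapy". The Background describes sequential GFR and SPECT measurements "undertaken before, during and after radiotherapy", whereas the timing aims in Study design and schedule mention only the periods before and following treatment. The inclusion criteria ask for more than 40 Gy in 4 weeks and set no number of fractions or maximum course length. Item iv of Data analysis plans a separate acute analysis of images taken before 12 weeks.

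**The concern.** There are two separate problems, both in how exposure is matched to response.

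First, an algorithm that is rewarded for making follow-up SPECT resemble baseline SPECT works against the contrast that the study wants to measure. Where function has been lost in a high-dose region, it can move neighbouring active tissue into the defect. This concerns every follow-up scan and the SPECT-based regional analyses (items i, ii and iv). The planned check, fitting on the first 20 datasets and predicting SPECT change in the next 10, would not reveal it, because both sets carry the same distortion.

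Second, a scan made before the course is finished reflects only the dose given so far. Pairing it with the full plan makes the kidney look more tolerant per Gy than it is. The same holds at every visit for a participant who stops radiotherapy early but keeps attending for scans.

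**Working it through.** The article gives no figure for either effect, so there is none to reproduce. Its sample-size figures do not depend on this point.

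**1. Direction of the registration effect**

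Let B be baseline SPECT, F follow-up SPECT and u the displacement. Suppose the software minimises

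J(u) = w_S·S(u) + w_C·C(u) + λ·R(u),

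where S is the summed squared difference between F(x + u) and B(x), C the CT mismatch, R a roughness penalty, and the weights are positive. Suppose also that, after bone alignment, the kidney has not moved, so that the correct answer is u = 0.

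- At the fitted û, J(û) ≤ J(0).
- The true alignment minimises the CT term and has no roughness: C(û) ≥ C(0) and R(û) ≥ R(0) = 0.
- Hence S(û) ≤ S(0).

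S is the total squared SPECT change, so under these assumptions the measured change cannot exceed the true change, and any displacement driven by SPECT reduces it. The CT term limits the loss but does not remove it. This gives a direction overall, not a guarantee for every region. The size depends on w_S, w_C, λ and the similarity measure, none of which is in the article.

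**2. Dose at the 4-week scan**

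Inputs: scan at 4 weeks from the first fraction (Study design and schedule); course length W weeks, not fixed in the article, so assumed to be 4 to 6; even delivery assumed.

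- Fraction delivered: f = min(1, 4/W).
- If loss in region j is β·f·D_j, where D_j is planned dose, regression on D_j gives slope β·f. Loss per Gy is understated by 1 − f.
- A dose-valued parameter, such as the dose for a given response, is inflated by the factor 1/f.

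| W (weeks) | f | Loss per Gy understated by | Dose parameter multiplied by |
|---|---|---|---|
| 4 | 1.00 | 0% | 1.00 |
| 4.5 | 0.89 | 11% | 1.125 |
| 5 | 0.80 | 20% | 1.25 |
| 5.6 | 0.71 | 29% | 1.40 |
| 6 | 0.67 | 33% | 1.50 |

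Simulation check, true slope −0.50 per Gy: with f = 0.80 for everyone, the slope on planned dose is −0.40 and the correlation is −0.253 with either dose. With f mixed over 0.67, 0.80 and 1.00, the slope is −0.41 and the correlation −0.258, against −0.272 with cumulative dose.

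**3. Reach**

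At 12 weeks and later, f = 1 for all these course lengths if treatment was completed. With five visits pooled at equal weight and a constant slope, the ratio is (f + 4)/5, which is 1.00 at W = 4 and 0.93 at W = 6. The acute analysis has no such dilution: read literally, it contains the 4-week scan alone.

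For an early stopper, f is fractions given divided by fractions planned, and it applies at every scan. Data collection and quality assurance excludes those who withdraw consent mid-treatment or have no further scans. It does not exclude someone who ends radiotherapy early and continues scanning.

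**The case against.** **On dose.** The inclusion criterion, read literally, puts more than 40 Gy in by week 4. A plan of 45 Gy would then be overstated by a factor below 45/40 = 1.125, and a 4-week course not at all. (45 Gy is the top of a colour scale in Figure 1, not a stated prescription.) The Background sentence about measurement during treatment describes the approach in general, and Study design and schedule points the other way. The first hypothesis concerns correlation, which a common scaling of dose leaves unchanged. The Background also describes the kidney response as late, between 3 and 18 months. All of this stands and limits the point. It does not settle how long courses are, and the acute NTCP and EUD fits have parameters in Gy. The early-stopper case is inferred from there being no other dose variable, and its frequency is unknown.

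**On stronger dose readings.** A reader might infer that every SPECT change is mis-dosed, or that any gap between plan and delivery pulls the slope to zero. Neither follows. Later scans of participants who complete treatment carry the right total. Random deviation of delivered from planned dose left a simulated linear slope at −0.497 against −0.50 (deviation SD 5 Gy assumed). A reader might also want to rebuild delivered dose from the positioning record: "Applied patient shifts will be recorded together with localisation images". Those shifts are on-line corrections back to the plan, so applying them to the dose would reintroduce errors already removed.

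**On registration.** The method uses CT as well as SPECT, Figure 2 is not shown, and registration on CT alone has its own error, which blurs dose gradients. This stands against any stated percentage of lost signal: a one-dimensional, SPECT-only illustration yields whatever its assumed stiffness dictates. It does not make an alignment driven by the outcome a sound basis for the main analysis.

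**Conclusion.** The point holds in two parts.

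1. The outcome image helps to drive its own alignment. The likely bias is toward a weaker regional dose-response. Its direction rests on a squared-difference criterion and a kidney that is correctly placed after bone alignment; its size cannot be derived from the article.
2. The dose variable does not match the stated target of delivered dose. The consequence is confined to the 4-week scan in courses longer than 4 weeks, and to all scans of early stoppers who keep attending. For the 4-week scan, the understatement of loss per Gy is 0% to 33% over assumed courses of 4 to 6 weeks with even delivery, and nil if treatment is complete by the scan.

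The first part matters more, since it reaches every follow-up scan. Both should be changed before the models are fitted. Neither shows that the correlation hypothesis cannot be tested, and neither affects the sample size.

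**What to change.** - **Registration.** Drive the deformable registration for the main regional analyses by CT anatomy and kidney contours, and report the combined CT and SPECT registration as a sensitivity analysis. Data collection and quality assurance describes the CT settings as adequate for defining organs and matching bone, so this is feasible. The cost is one further registration per follow-up scan, at most 5 × 30 = 150 for 30 complete datasets, in a study that already calls 30 its limit of manageability. The downside is noisier alignment at the kidney edge.
- **Dose.** Define the dose variable as plan dose multiplied by the share of planned fractions actually delivered up to each scan. This handles the 4-week scan and early stoppers together, and equals the plan wherever treatment is complete. Fraction counts should be in the treatment record (an assumption; the article does not list them).
- **Text.** Reconcile the Background, which has measurements during radiotherapy, with Study design and schedule, which has them only before and following it, and state whether the 4-week scan can fall within treatment.

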**Figure 2 F2:**
[figure not shown]
Diagram of the co-registration method.

This subsequent analysis of co-registered dose and image data will be undertaken in several ways:

i. Methods will be developed to assess dose-response correlations as a function of spatial position across each kidney (sampled at varying resolutions). Kidney volumes will be uniformly divided into regions on the three-dimensional (3D) grid defining image and spatially-registered radiation dose. t-tests and Wilcoxon signed-rank tests will be undertaken to determine regions with significantly different mean SPECT-signal intensities between time-points for each study participant. Mixed modelling with repeated measures (and random subject effect) will be conducted across all participant sets to examine the correlation of local radiation dose with SPECT signal changes, generating a map of dose-response change across all kidney volumes. Given a significant correlation, this will be extended to incorporate any revealed patterns of co-morbidity or adjuvant therapy as categorical variables.

ii. Dose-response correlations will then be examined according to structural and functional regions. Analysis i. will be repeated, but with regions defined according to kidney structure, with medulla, renal artery and cortex regions treated independently. This will also involve cross-correlation between these regions to examine inter-play that is likely to arise due to the influence of radiation effects on vascular structures.

iii. Spatio-temporal mathematical models of functional kidney dose-response will be implemented to relate regional kidney irradiation to the primary measure of total kidney function, GFR. These models, including percolation theory [25] and the critical functioning volume model of Rutkowska et al [26], will utilise the 3D radiotherapy dose distribution (both across each kidney and across individual functional regions) to fit model parameters using maximum likelihood estimation (MLE) methods. The statistical assessment of fitting will be made by assessment of parameter confidence intervals, and by undertaking an F-test of the residual sums-of-squares from MLE against that from MLE for a simple linear (single-parameter) dose-response model.

iv. An export of co registered dose and SPECT information will be made for regions defined by whole kidneys, separately-identified medulla and cortex, baseline-image functional regions, and at varying spatial resolutions. Renal response patterns obtained from variations in SPECT and GFR shall be fitted to normal-tissue complication probability (NTCP) and equivalent uniform-dose (EUD) models, as previously undertaken by CI’s using estimated parameters [27,28]. Response indicators can be related to dose volume histogram (DVH) and dose-function histogram (DFH) data by maximum likelihood fitting to the parametric NTCP/EUD models. For this purpose, the freely available DREES code [29], developed in Matlab, will be utilised. Separate analyses will be undertaken using acute changes in SPECT signal (< 12 week images) as well as the long-term changes indicated by images taken at 52 or 78 weeks post-radiotherapy.

Examination of the predictive nature of response models will be made by establishing parameters based on the first 20 patient data sets, and utilising the models to predict SPECT signal changes on the subsequent 10 patients. In order to minimise parameter uncertainties however, final parameter values will be based on data for all patients.

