## Methods/design

### Study design and schedule

RAPRASI is a clinical research study for participants with upper gastrointestinal malignancies (without metastatic disease) and who have controlled and stable kidney function. Radiotherapy treatment technique is according to local departmental protocols. Participants are being recruited as they present to the Department of Radiation Oncology, Sir Charles Gairdner Hospital (SCGH) in Perth, Australia, and to the Department of Radiation Oncology, Peter MacCallum Cancer Centre (PMCC) in Melbourne, Australia. The protocol has been approved by both institutional ethics committees. All patients are required to give written informed consent.

In addition to a baseline visit, timed to coincide with participants having a CT scan for the purpose of radiotherapy simulation, participants will have follow-up visits at 4, 12, 26, 52 and 78 weeks subsequent to the first radiotherapy treatment fraction. On each occasion they will undergo: a sequential ^99m^Tc-DMSA SPECT/CT (simultaneous SPECT and CT images), a GFR measurement (^51^Cr-EDTA clearance), a full blood count and assessment of blood urea and electrolytes.

The timing of SPECT/CT scans is intended to reveal i) acute and sub acute changes in total kidney function (GFR measurement) before and following radiotherapy, ii) information on kidney positioning before and following radiotherapy, and iii) the time-dependence of changes in regional kidney function and position (SPECT/CT scans) before and following treatment.

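### Per-participant tests for changed regions have only the pixels of one scan per time-point as replicates, so their p-values are too small

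*Protocol article*

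**What the plan says.** All references are to the Protocol article.

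- **Data analysis, analysis i (listed after Figure 2).** "Kidney volumes will be uniformly divided into regions on the three-dimensional (3D) grid", and dose-response is assessed "as a function of spatial position across each kidney (sampled at varying resolutions"). Then "t-tests and Wilcoxon signed-rank tests will be undertaken to determine regions with significantly different mean SPECT-signal intensities between time-points for each study participant". A mixed model with repeated measures and a random subject effect follows as a separate step across all participants.
- **Analysis ii.** "Analysis i. will be repeated, but with regions defined according to kidney structure": medulla, renal artery and cortex.
- **Study design and schedule.** After a baseline visit, "participants will have follow-up visits at 4, 12, 26, 52 and 78 weeks subsequent to the first radiotherapy treatment fraction". Every visit, baseline included, has one DMSA SPECT/CT. No repeat scan at the same time-point is described.
- **Data collection and quality assurance.** The scanner is described as "providing 128x128 pixel attenuation-corrected images reconstructed at approximately 5 mm pixel resolution", with OSEM reconstruction and intensities normalised from monthly calibration images. Five changes are listed, each from baseline.
- **Data analysis, opening paragraph.** Follow-up scans are normalised for administered activity and deformably registered to the baseline scan.
- **Statistical considerations.** The only power calculation is a paired t-test with a measurement error of 20% and patients as the unit.

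**The concern.** A test of whether a region's mean changed between two time-points needs an error term that reflects how much that mean would vary between two scans with nothing happening to the kidney. One participant with one scan per time-point gives no estimate of this. The test can still be computed by treating the region's pixels as independent observations, but they are not independent. Blur makes neighbouring pixels move together. An error in the measured activity, the calibration or the registration moves a whole region together. The test then measures pixel noise within a pair of scans and reports it as evidence of change in the tissue.

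What is at stake is any statement that a given region of a given patient's kidney changed significantly. In a study about regional response, such statements would be read as findings.

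**Working it through.** **1. The plan's own figure.** Inputs from Statistical considerations: reduction 10%, error 20% (taken as the SD of the paired difference), alpha 0.05 (taken as two-sided), power 80%. Normal approximation: (1.96 + 0.84)² × (20/10)² = 31.4. Noncentral t: 33.4, with power 79.5% at 33 and 80.8% at 34. Detectable with 30 patients: 10.6%. The stated 33 and 10.5% therefore reproduce closely. They describe a test with patients as replicates and say nothing about the error rate of a test inside one patient.

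**2. What can serve as a replicate.** Analysis i fixes the test, the quantity (a region's mean), the contrast (between time-points) and the unit (each participant). With one scan on each side of the contrast, only pixels remain. Using regions as replicates would test the whole kidney and could not say which region changed.

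**3. Effect of blur alone.** The article gives neither blur nor region size, so both are assumed. Method: Gaussian-smoothed noise on a 5 mm grid with no true change; one-sample t-test and signed-rank test on the pixel differences; 2,000 runs per setting. Rejection rates at nominal 0.05 for a region of 5 × 5 × 5 = 125 pixels:

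| Blur, FWHM | t-test | Signed-rank |
|---|---|---|
| none | 4% | 4% |
| 1.5 pixels (7.5 mm) | 49% | 47% |
| 2 pixels (10 mm) | 65% | 64% |
| 3 pixels (15 mm) | 79% | 78% |

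The first row shows that the simulation behaves when pixels are independent. Region size matters: over 8 to 216 pixels the t-test rate is 34–48% at 7.5 mm, 52–65% at 10 mm and 68–80% at 15 mm. The lowest rate over all blurred settings is 31% (signed-rank, 8 pixels, 7.5 mm).

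**4. Effect of a shared scan-level error alone.** Let ρ be the share of a pixel difference's variance that is common to the whole region, and n the number of pixels. The t statistic is inflated by k = √[(nρ + 1 − ρ)/(1 − ρ)], and the true error rate is 2·P(T > t_crit/k) on n − 1 degrees of freedom.

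- n = 64, ρ = 0.05: k = √(4.15/0.95) = 2.09; t_crit/k = 2.00/2.09 = 0.96; error rate 34%.
- n = 64, ρ = 0.20: k = √(13.6/0.8) = 4.12; t_crit/k = 0.48; error rate 63%.

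So a small shared error is enough, even with no blur.

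**5. Would a multiplicity correction repair it?** Assume 8 regions × 2 kidneys × 5 comparisons with baseline = 80 tests per patient. The Bonferroni level is 0.05/80 = 0.000625. In the simulation of step 3 the t-test at that level still rejects 20%, 41% and 62% of the time at blur of 1.5, 2 and 3 pixels. In step 4 with n = 64 and ρ = 0.05 it rejects 9% of the time (3.60/2.09 = 1.72). The correction presupposes valid p-values, and these are not valid.

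**The case against.** **The pixel as unit is inferred.** The article never names the pixel as the test unit, and analysis i opens by saying that methods are still to be developed. The phrase about each participant could be stretched to mean pairing within patients in a group-level test. This lowers certainty a little. But the per-participant reading is the natural one, and under it no other replicate exists. The article also does not say whether the t-test is paired; the figures above are for paired pixel differences, which the signed-rank test requires anyway.

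**The main inference lies elsewhere.** This stands, and it limits the point. Dose-response across patients rests on the mixed model, which uses signal changes. A reader might infer that the flagged regions feed that model, or the renal response patterns fitted to NTCP and EUD models. The article does not say so: those fits use exported dose and SPECT data, with no significance filter mentioned.

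**The absent multiplicity rule.** A reader might count this as a fault in itself. It may sit in an analysis plan that is not shown, so it is not counted here.

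**Most flagged regions are false.** A reader might infer this from the error rates. With α the true error rate and power 80%, it holds only if the share of regions truly changed is below α/(α + 0.8): 33% for α = 0.4, 43% for 0.6, 50% for 0.8. The documents do not give that share, and these patients do receive kidney dose. It is possible, not shown.

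**A repeatability threshold.** It is tempting to turn the 20% in Statistical considerations into a limit for one region's change. The article uses that figure in a patient-level calculation and does not present it as one region's repeatability.

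**Conclusion.** The point holds for the per-participant regional tests in analysis i and their repeat in analysis ii. As worded, they can only use pixels as replicates, and their nominal 5% error rate is then not 5%. It is about 45 to 80% for a 125-pixel region with blur of 1.5 to 3 pixels, and about 31 to 34% for the smallest region at the least blur tried. Blur, region size and the size of any shared scan-level error are assumptions. The direction does not depend on them: any positive correlation between pixels makes the p-values too small, and replacing the t-test by the signed-rank test gives no protection.

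The consequence is confined to claims of significant change in single patients. Neither the sample size nor the across-patient dose-response analysis is shown to depend on them. Severity: should be fixed.

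**What to change.** - In analyses i and ii, remove the per-participant t-tests and signed-rank tests. Present each participant's regional changes from baseline as descriptive maps, without p-values or significance labels.
- State that inference about regional change and about dose-response comes only from the across-patient mixed model, with the patient as the independent unit and regions nested within kidney and patient.

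**Cost.** A change of wording; no new data, and the mixed model is already planned. The real loss is that no region can be called significantly changed in a single patient. Keeping such a claim would need an estimate of scan-to-scan repeatability for a region, and with one scan per visit the study as described does not collect it.
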